#### 10.1.1 Set-up Visit

The study monitor or PVS representative will contact the site prior to the start of the study to discuss the protocol and data collection procedures with site personnel. Prior to enrollment of subjects at the study site, specific regulatory documents must be available, including approvals from the independent ethics committee (IEC) at the Russian Ministry of Health and from institutional review boards of the participating institutions (see Section 1). Curriculum vitae for key investigators must also be available. PVS will inform the investigator of any additional documents that need to be provided.

#### 10.1.2 Follow-up Visits

Monitoring will be conducted according to PVS's requirements. The individuals responsible for monitoring the study will periodically review the progress of the study and should have access to all records necessary to ensure the ethical and safety conduct of the study and the integrity/validity of the recorded data.

During sites visits and contacts, the monitor will:

- Check and assess the progress of the study.
- Review study data collected.
- Perform source data verification.
- Review regulatory files.
- Identify any issues and address their resolution.

This will be done in order to verify that:

- The data are authentic, accurate and complete.
- The safety and rights of subjects are being protected.
- The study is conducted in accordance with the approved protocol (and any subsequent amendment) and all applicable regulatory requirements.

As part of study conduct, the principal investigator agrees to allow the monitor or PVS representative direct access to all relevant documents and to allocate his/her time and the time of his/her staff to the monitor to discuss findings and any relevant issues.

The principal investigator also agrees to allow representatives of IEM and/or Microgen to occasionally accompany the monitor or PVS representative during site visits.

### **10.1.3 Close-out Visit**

Upon completion of the study, the study monitor or PVS representative and the investigator will conduct the following activities:

- Data clarification and/or resolution
- Accounting, reconciliation and destruction at sites of used and unused vaccines
- Review of site study records for completeness
- Return of all study data to PVS

PVS and Sponsor retain the right to temporarily suspend or prematurely discontinue this study at any time related to safety. If the study is stopped or suspended prematurely, PVS will inform the local principal investigator as well as regulatory authorities about the decision and the reasons for termination or suspension. If such action is taken, all efforts must be made to ensure the safety of the subjects enrolled in the study and the safety of the local community. The principal investigator will assist the Sponsor, Microgen, in informing the responsible IEC and provide the reason for the suspension or termination. In case of premature study or study site closure, the monitor or PVS representative will conduct all activities as indicated above.

## **10.2 Audits and Inspections**

For the purpose of compliance with applicable regulatory guidelines it might be necessary for PVS or national or foreign regulatory authorities to conduct a site audit. This could occur at any time from start to after conclusion of the study.

The principal investigator agrees to allow the auditor direct access to all relevant documents and to allocate his/her time and the time of his/her staff to the auditor to discuss findings and any relevant issues.

National and foreign regulatory authorities may conduct a regulatory inspection of this study. If a regulatory authority requests an inspection, the principal investigator must inform PVS immediately about this request. The principal investigator agrees to allow the inspector(s) direct access to all relevant documents and to allocate his/her time and the time of his/her staff to the inspector(s) to discuss findings and any relevant issues.

## **10.3 Archiving**

In accordance with applicable regulatory requirements, following closure of the study, the investigator/institution will maintain a copy of study documents in a secure and designated location at the study site. Essential documents shall be retained for at least five (5) years after the completion or discontinuation of the study.

## **11 Statistical Considerations**

The data analysis for this study will be conducted primarily by PVS in Seattle, Washington. For the purpose of analysis of the primary safety objectives, the clinical trial database will not be unblinded until the database has been frozen, and the statistical report table shells generated and completed. The Sponsor and PI will participate in the review and approval of the data analyses.

### **11.1 Study Hypotheses**

There are no pre-set statistical hypotheses to be tested in this trial. All objectives are descriptive. As such, no sample size is calculated. Total numbers to be enrolled in the trial are consistent with those of phase 1 vaccine trials.

### **11.2 Definition of Analysis Sets**

All primary safety descriptions and summaries will be performed on an intention-to-treat basis. Supportive per-protocol analyses will also be conducted on all enrolled participants who are randomized, receive two doses of study vaccines and complete the Day 56 visit.

### **11.3 Analysis Plan**

A complete Data Analysis Plan with table shells will be generated and finalized prior to freezing of the database and prior to unblinding of the statistician.

#### **11.3.1 Safety**

The safety profile will be parameterized as the proportion of subjects experiencing adverse events (AEs) of the following four categories:

- Immediate reactions occurring within two hours of administration of any dose, measured as observed by study staff or reported by the subject to study staff.
- Adverse events commonly associated with intranasal vaccination (solicited local and systemic reactions) occurring greater than two hours after administration of any dose of study vaccine or placebo through 7 days following any dose, measured as observed by study staff or reported by the subject to study staff.
- All other adverse events (including unsolicited events) occurring during the 7 days following any dose, measured as observed by study staff or reported by the subject to study staff. This includes abnormal laboratory findings from blood and urine specimens collected on Days 7 and 35.
- All serious adverse events (SAEs) occurring within 4 weeks of receipt of any dose, as observed by study staff, reported by the subject to study staff, or noted by the subject on a diary card. This includes abnormal laboratory findings from blood and urine specimens collected on Days 28 (pre-vaccination) and 56.

Counts of all events will be reported and summarized according to event severity, as “any local AE”, or “any systemic AE”, and by relationship to administration of study vaccine or placebo, as deemed by a blinded study clinician. Percentages of subjects experiencing each reaction or event or at least one reaction or event will be calculated along with 95% confidence intervals (CIs) using exact statistical methods.

No multiplicity adjustment to the error rate, alpha, will be made because there are no statistical hypotheses and all analyses will be descriptive.

### **11.3.2 Immunogenicity**

Immune responses will be parameterized as the proportion of subjects with at least a four-fold rise after each dose from baseline or as the mean titer after each dose in any of the following:

- Serum hemagglutination inhibition (HAI) antibodies
- Serum neutralizing antibodies using microneutralization assay
- Serum IgA and IgG by EIA
- Mucosal IgA antibodies in nasal wick specimen

Virus shedding will be parameterized as the proportion of subjects shedding virus (detected by real-time reverse transcriptase polymerase chain reaction (rRT-PCR) in nasal or conjunctival swabs or by isolation in chicken embryos) at any time-point. Shedding data will be reported for every subject at every measured time-point.

Percentages of subjects with each immune response will be calculated along with 95% CIs using exact statistical methods. Geometric mean titers (GMTs) along with 95% CIs will also be calculated using the t-test. No multiplicity adjustment to the error rate, alpha, will be made because there are no statistical hypotheses and all analyses of immunogenicity will be descriptive. It is not expected that any subject will have measureable baseline titers to H7. Thus, no screening will be done based on serologic status. However, during analysis, any subject with baseline titer to H7 of >1:20 may be excluded from the immunogenicity analysis or the immunogenicity analysis will be stratified.

Cellular immune responses (cytokine and T-cell) will also be measured using isolated PBMCs tested by flow cytometry and/or ELISPOT assay. These analyses will be exploratory and descriptive only.

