#### **3.1.2 Secondary and Exploratory Objectives:**

To describe the post-vaccination serologic immune responses to influenza vaccine.

To describe the post-vaccination shedding of vaccine virus and genetic stability of any shed virus.

Exploratory: To describe the post-vaccination cellular immune responses to influenza vaccine.

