### **3.2.2 Secondary Outcome Measures**

Immune responses will be parameterized as the proportion of subjects with at least a four-fold rise after each dose from baseline or as the mean titer after each dose in any of the following:

- Serum hemagglutination inhibition (HAI) antibodies
- Serum neutralizing antibodies
- Serum immunoglobulin class A (IgA) or immunoglobulin class G (IgG) antibodies measured by enzyme-linked immunoassay (EIA)
- Mucosal IgA antibodies in nasal wick specimen

Virus shedding will be parameterized as the proportion of subjects shedding virus [detected by real-time reverse transcriptase polymerase chain reaction (rRT-PCR) in nasal or conjunctival swabs or by isolation in chicken embryos] at any time-point. Shedding data will be reported for every subject at every measured time-point. Molecular characterization of any isolated shed virus will be reported with sequence details of any loss of attenuation mutations.

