## **6 Study Products**

### **6.1 Study Product Descriptions**

#### **6.1.1 Study Vaccine**

Study vaccine for this trial is a cold-adapted, live attenuated monovalent A/17/mallard/Netherlands/00/95(H7N3) influenza vaccine. The virus strain in this vaccine was constructed in the laboratories of IEM by classical reassortment of A/mallard/Netherlands/12/00(H7N3) virus with a cold-adapted temperature sensitive A/Leningrad/134/17/57(H2N2) virus master donor strain in developing chicken embryos. The 6:2 genomic reassortant was characterized for acceptable phenotype and genotype [presence of cold-adapted, temperature sensitive, HA, and NA markers], with genetic sequencing used to confirm the molecular basis of the attenuated phenotype. The developed vaccine strain was transferred to Microgen, to produce a bulk lot of vaccine for use in preclinical immunogenicity and challenge studies and for use in clinical trials. Manufactured vaccine was obtained from virus-containing allantoic fluid of chicken embryos. Microgen has transferred the manufactured vaccine back to IEM where it has been securely stored.

LAIV H7N3 is a lyophilizate (a light yellow-colored amorphous mass) of live attenuated influenza virus for the preparation of a solution for intranasal introduction. The active component is the vaccine strain A/17/Mallard/Netherlands/00/95(H7N3) virus obtained from the allantoic fluid of chicken embryos. LAIV H7N3 is supplied lyophilized in single-dose ampoules [specific activity of the vaccine is not less than 7.5 log EID50/0.5 ml dose]. The lyophilizate also contains the following stabilizers: sucrose, lactose, glycine, sodium glutamate, tris (hydroxymethyl) amino-methane, sodium chloride, and gelatin.

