#### 8.2.2 Special Assays

***Procedures for all laboratory assays will be specified in detailed protocols maintained at the either RII or IEM.***

##### 8.2.2.1 Detection of Shed Virus by rRTPCR

Nasal swab (and conjunctival) swab specimens will be tested for evidence of influenza virus using rRTPCR. These assays will be conducted by RII.

Nasal swab specimen collection for this purpose will occur daily on Days 0-7 and Days 28-35, while a subject is admitted to the isolation unit. Collection must occur both prior to and at least 6 hours after administration of study vaccine or placebo on Days 0 and 28. For nasal swabs collected on Days 1-6 and Days 29-34, results (influenza A positive or negative) of testing for a subject must be complete and determinant within 30 hours of specimen

collection. For nasal swabs collected on Day 7 and Day 28, results (influenza A positive or negative) of testing for a subject must be complete and determinant by 16:00 on that day. Confirmation of subtype should occur within 72 hours of specimen collection.

Conjunctival swab specimen collection will occur only for those subjects who develop conjunctivitis. Conjunctival swab specimens will be collected only on the first day of appearance of conjunctivitis. Results (influenza A positive or negative) of testing for a subject must be complete and determinant within 30 hours of specimen collection. Confirmation of subtype should occur within 72 hours of specimen collection.

Nasal swab specimens collection for rRTPCR testing will only occur past Day 7 or past Day 28 if a subject is requested to remain admitted to the isolation unit because a nasal (or conjunctival) swab specimen was influenza A positive during the final two planned days of stay in the isolation unit after each dose (Days 6 or 7 or Days 34 or 35).

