## 9.5 Halting Rules

Given the long experience with LAIVs, no safety issues are anticipated which would result in the suspension of the study. However, as this study is a phase 1 trial, the trial might be suspended at any time by the Sponsor, PVS, the Russian Ministry of Health, the SMC, any ethical review committee overseeing this study, or by the investigator for any safety concern. This includes, for example, and without limitation, an SAE resulting in death, an unexpectedly high number of persons shedding virus after receipt of any dose, an unusually high rate of SAEs, or an unexpectedly early onset of substantial seasonal influenza virus circulation in the surrounding community. PVS may suspend the study in the event that study conduct is found to be below GCP standards.

Should an SAE occur which is likely related to administration of study vaccine, the decision whether the study should continue per protocol, proceed with caution, be suspended pending further investigation, be discontinued, or be modified and then proceed will be made by the Sponsor and PVS in consultation with the investigators, the SMC, and/or the RF MoH. However, no rules will be prespecified to define these conditions.

If the study is halted, subjects will be contacted immediately explaining why the study has been halted and the implications for their medical well-being.

In the event of the appearance of new data that indicate an increased level of risk to participating subjects, the clinical trial will be suspended until the Sponsor, PVS, the Russian Ministry of Health, the SMC, and all ethical review committees have reviewed relevant data and agreed that the trial may proceed.

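### The shedding proportion has no post-dose start and no H7 requirement, so as worded it can count the Day 0 pre-dose swab and residual spray at 6 hours

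*Protocol*

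**What the plan says.** Protocol section 3.1.2 states the objective: "To describe the post-vaccination shedding of vaccine virus and genetic stability of any shed virus". The endpoint is set in section 3.2.2, "Virus shedding will be parameterized as the proportion of subjects shedding virus", and again in section 11.3.2, where detection by rRT-PCR counts "in nasal or conjunctival swabs or by isolation in chicken embryos) at any time-point". The Protocol Summary uses the same rule, although it also says that shedding is assessed after each dose. Sections 3.2.2 and 11.3.2 promise results for each subject at each measured time-point.

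Section 8.2.2.1 lists the rRT-PCR swabs: "Nasal swab specimen collection for this purpose will occur daily on Days 0-7 and Days 28-35", and for dosing days "Collection must occur both prior to and at least 6 hours after administration of study vaccine or placebo on Days 0 and 28". The Trial Scheme and sections 7.2.1 and 7.2.10 repeat both dosing-day swabs. The routine read-out is influenza A positive or negative, followed by subtyping: "Confirmation of subtype should occur within 72 hours of specimen collection". The virological assay text under section 8.2.2.2 names a test that identifies H7. Egg isolation uses only swabs from Days 1, 2, 3, 5, 7, 29 and 31.

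On the dose, section 6.1.1 says "specific activity of the vaccine is not less than 7.5 log" EID50 per 0.5 ml. Section 6.1.2 describes a placebo made from uninoculated allantoic fluid.

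**The concern.** The objective concerns vaccine virus that the subject sheds after vaccination. The endpoint has no start time and no subtype condition, so two kinds of result that are not evidence of such shedding can enter the numerator.

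The first is a positive Day 0 pre-dose swab, which cannot be vaccine virus. The second is a swab taken about 6 hours after a large dose was sprayed into the same nasal passages. rRT-PCR detects RNA, whether it was deposited or replicated, and H7 subtyping does not help because the inoculum is itself H7. Carry-over arises only in vaccinees, so the placebo arm gives no correction for it.

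Section 2.1 explains why shedding matters: it could influence the propensity to reassort with human strains, and related vaccines are described as highly restricted in replication. A proportion that one carry-over positive can satisfy is a poor summary for that question.

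Separately, the H7 result is planned but the endpoint does not say that it is required.

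**Working it through.** The protocol states no shedding rate, sample-size calculation or assay limit, so there is no figure to reproduce. The check has three parts.

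**1. Which swabs qualify.** Planned rRT-PCR nasal swabs per subject, from section 8.2.2.1 and the Trial Scheme:

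| Swab | Number | Can a positive show replicated vaccine virus? |
|---|---|---|
| Day 0 pre-dose | 1 | No |
| At least 6 h post-dose, Days 0 and 28 | 2 | Not separable from inoculum by rRT-PCR |
| Day 28 pre-dose | 1 | Yes, as persistence after dose one |
| Days 1–7 and 29–35 | 14 | Yes, though the next-morning swab may still carry inoculum |

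The total is 1 + 2 + 1 + 14 = 18. Four of 18 (22%) fall on dosing days. No text excludes any of them from the endpoint. None of the four feeds egg isolation, so the problem is confined to the rRT-PCR component.

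**2. Possible size of the carry-over effect.** Section 4 gives 9 + 21 = 30 vaccinees and 3 + 7 = 10 placebo subjects. Let p be the proportion who truly shed. Let r be the chance that a vaccinee has a 6-hour positive from inoculum alone, taken as independent of p. Both are assumptions. Then

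counted proportion = 1 − (1 − p)(1 − r).

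For p = 0.40 and r = 0.3: 1 − 0.60 × 0.70 = 0.58, or about 17 of 30.

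| True p | r = 0.1 | r = 0.3 | r = 0.5 | r = 0.9 |
|---|---|---|---|---|
| 0.20 (6/30) | 0.28 (8/30) | 0.44 (13/30) | 0.60 (18/30) | 0.92 (28/30) |
| 0.40 (12/30) | 0.46 (14/30) | 0.58 (17/30) | 0.70 (21/30) | 0.94 (28/30) |
| 0.60 (18/30) | 0.64 (19/30) | 0.72 (22/30) | 0.80 (24/30) | 0.96 (29/30) |

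Exact 95% intervals for p = 0.40:
- without carry-over, 12/30: 22.7–59.4%
- r = 0.1, 14/30: 28.3–65.7%
- r = 0.3, 17/30: 37.4–74.5%
- r = 0.5, 21/30: 50.6–85.3%
- r = 0.9, 28/30: 77.9–99.2%

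At r = 0.5 the interval already lies wholly above the assumed true 40%. At r = 0.1 the distortion is small beside the sampling error.

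**3. Incidental influenza A, only if the H7 result were not applied.** With an assumed infection risk s, the chance of at least one positive among 10 placebo subjects is 1 − (1 − s)^10. This gives 9.6% at s = 0.01, 40.1% at s = 0.05 and 65.1% at s = 0.10. The expected number among 30 vaccinees is 30s: 0.3, 1.5 and 3.0.

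**The case against.** Several points on the other side stand.

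- **Seasonal influenza.** A reader might infer that seasonal infections are counted as vaccine-virus shedding. No section says so. The objective names vaccine virus, H7 subtyping is planned, and isolates are typed and sequenced. The generic influenza A read-out is a laboratory turnaround requirement that serves discharge decisions. Section 9.5 lists "unexpectedly early onset of substantial seasonal influenza virus circulation in the surrounding community" as an example of a reason to suspend. What remains is a missing explicit link between endpoint and subtype.
- **Day 28 pre-dose swab.** It is not a pre-vaccination sample. An H7 positive there could be real persistence after dose one.
- **Other data on replication.** A reader might infer that the trial cannot address replication at all. Egg isolation avoids every dosing-day swab, positives are titrated, and the by-time-point listing lets anyone recompute a restricted proportion. The defect lies in the summary proportion.
- **Suspension.** A reader might infer that an inflated proportion would halt the trial. Section 9.5 mentions an unexpectedly high number of shedders as an example for judgement, gives no threshold and does not refer to this endpoint.
- **Magnitude.** A reader might infer a result near 30/30 with no replication at all. That needs an assumed carry-over rate close to 1, which the protocol neither gives nor excludes.
- **Data Analysis Plan.** Section 11.3 promises one before unblinding, and it could set windows. It would then be narrowing a rule that the protocol states in three places, so the protocol wording is where the correction belongs.

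**Conclusion.** The point holds in a limited form. As worded, the rRT-PCR part of the shedding proportion admits the Day 0 pre-dose swab, which contradicts the objective. It also admits the two 6-hour swabs, where inoculum and replicated virus cannot be separated. Inoculum can bias the result only upward and only in the vaccine arm. Its size cannot be derived from the protocol: over the assumed r of 0.1 to 0.9, a true 40% would be counted as 46% to 94%. The endpoint should also name the H7 result on which it implicitly relies.

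This is a secondary, descriptive endpoint, no data are lost, and section 11.1 sets no hypothesis. It should be fixed, but it does not put the trial's primary safety outcome in doubt.

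**What to change.** In section 3.2.2, section 11.3.2 and the Protocol Summary, define vaccine-virus shedding separately after each dose. It should be an H7-confirmed rRT-PCR positive, or an egg isolate, from a swab taken from Day 1 onward (dose one) or Day 29 onward (dose two). Add a sensitivity summary from Day 2 or Day 30 onward, because section 7.2.2 schedules the Day 1 swab for the morning after dosing and it may still carry inoculum.

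Report the remaining results separately:
- 6-hour swabs, as their own line
- the Day 0 pre-dose swab, as baseline
- an H7 positive on the Day 28 pre-dose swab, as possible persistence after dose one
- non-H7 or unsubtypable influenza A positives, as a separate listing

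The window and the H7 condition are both needed. The window deals with the spray, which is itself H7, and the H7 condition deals with other influenza A.

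The cost is wording only, since every swab and the subtype test are already planned. Isolation and discharge procedures are not affected. The downside is that true shedding seen only at 6 hours, or weak positives that cannot be subtyped, leave the main proportion. They remain visible in the by-time-point listing.
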